### 8.1.3 Other study parameters

Not applicable

## 8.2 Assignment to study

Patients eligible for surgery, according to inclusion- and exclusion criteria, will be assigned to either standard preoperative care or the multimodal intensive prehabilitation program, depending on the time frame and cluster in which the patient is included.

## 8.3

## 8.4 Study procedures

Study procedures are performed in the Radboudumc departments of Surgery, Urology, Neurosurgery, Orthopaedics, Head and neck surgery, Plastic surgery, Cardiothoracic surgery, and Gynaecology, as well as in the research lab of the department of surgery. Life style assessment and questionnaires will be taken before surgery and post operatively up to one year. An overview of all measurements performed during this stepped-wedge cluster randomized trial are demonstrated in Appendix I.

- The Clavien-Dindo classification is correlated with the complexity of the operation as well as the length of hospitalization and may be used internationally as quality screening for surgery(42, 43). The Comprehensive Complication Index summarizes the postoperative wellbeing of the patient concerning complications based on the Clavien-Dindo classification(44). The CCI-score is easily assessed at [www.assessurgery.com](http://www.assessurgery.com). Both scores will be determined at four weeks after surgery.
- Screening for physical fitness will be done according to the American College of Sports Medicine's (ACSM) guidelines for Exercise Preparticipation Health Screening (45) to assess whether high intensity interval (HIT) training during prehabilitation is safe. The screening process is based on current levels of structured physical activity, the presence of major signs or symptoms suggestive of cardiovascular, pulmonary or metabolic diseases, and desired exercise intensity. These guidelines require the exercise professional to 1) complete a cardiovascular risk factor profile; 2) determine if the patient has known cardiovascular, pulmonary, and/or metabolic diseases; and 3) identify major signs or symptoms suggestive of cardiovascular, pulmonary, and/or metabolic diseases. With this information a patient is classified as low, moderate, or high risk. Patients screened at high risk will be referred to a cardiologist or pulmonologist to get medical clearance for HIT training during prehabilitation. The exercise preparticipation health screening questionnaire for exercise professionals(46), developed to simplify the ACSM guidelines, will be performed prior to start of the prehabilitation program.
- The submaximal Astrand-Rhyming test will be used to estimate a patient's cardiorespiratory fitness. It is a simple, 6-minute, non-maximal cycle ergometer test(47) and therefore safer and better tolerated than maximal testing procedures, irrespective of the accuracy of the VO2 peak prediction(48).

- The indirect 1 repetition measures (1RM) are used to dose the training and will be determined based on chest press and leg press to assess the impact of the intervention throughout the perioperative period(49). The 1RM is calculated by the Brzycki formula:  $1RM = W \cdot 36 / (37 - r)$  (w=weight, r=repetitions)(50).
- The Patient-Generated Subjective Global Assessment (PG-SGA) screening tool will be used to identify malnutrition. This is an internationally validated instrument and preferred screening method to identify malnutrition in oncologic patients(20, 51-54). The energy requirements of the patient. Is calculated by the WHO formula.. Håkonsen et al recommended the PG-SGA as a nutritional assessment tool in colorectal cancer patients in combination with other parameters(55). The PG-SGA consists of two parts: 1) the first part is the Patient Generated Subjective Global Assessment Short Form (PG-SGA SF) which includes a brief questionnaire addressing current weight, weight history, acute weight changes, changes in food intake over the past month, occurrence of nutrition impact symptoms experienced over the previous 2 weeks and changes in physical activities and functions over the previous month. The PG-SGA SF will be completed by patients themselves and generates a score for nutrition risk. The PG-SGA SF is a widely validated malnutrition screening tool in cancer patients(56). 2) the second part will be completed by the dietician and includes a physical examination, where fat and muscle stores an fluid status are assessed, and assessment of the disease/ condition and metabolic demand. The global PG-SGA generates a subjective category rating for nutritional status: well-nourished (PG-SGA A), suspected malnutrition or moderate malnutrition (PG-SGA B), or severe malnutrition (PG-SGA C). It also provides a numeric score used for triaging nutritional intervention, i.e. to indicate the need for protein andcalorie (en)rich(ed) diet. PG-SGA will be measured at baseline and 1 week before surgery.
- For a first impression of body composition and function, a minimal set of anthropometric measurements are performed. Body weight and height are measured. With these measurements, body frame can be determined, and Body Mass Index (BMI, body weight (kg)/ (length) can be calculated. . Measurements will be carried out according to the Anthropometry Procedures Manual of the National Health And Nutrition Survey(57). Body weight and length will be measured at baseline and 1 week before surgery.
- Fat-free mass will be assessed using Bioelectrical impedance analysis (BIA), which is a non-invasive, commonly used method for estimating body composition. BIA allows the determination of the fat-free mass and total body water using appropriate population, age or pathology-specific BIA equations and established procedures(58). BIA will be performed at baseline and 1 week before surgery.

- During the dietetic assessment a 3-day food diary is used to obtain information about patients' food intake. To be able to estimate energy and protein intake, it is sufficient to record food consumption for a period of 3 days, including 2 weekdays and 1 weekend day (59).
- Psychological factors that may affect postoperative outcomes adversely will be identified by the Hospital Anxiety and Depression Scale (HADS). The Hospital Anxiety and Depression Scale (HADS) is developed to identify possible and probable anxiety disorders and depression among patients in nonpsychiatric hospital clinics(60). Physical symptoms, such as dizziness, headaches, insomnia, anergia and fatigue are excluded to prevent noise from somatic disorders. HADS is a validated screening tool for depression and anxiety in different groups of Dutch subjects(61) and is commonly used. HADS will be performed prior to the prehabilitation program to screen whether psychological support during prehabilitation could be of added value.
- Physical activity level will be measured through the Short Questionnaire to Assess Health-enhancing physical activity (SQUASH)(62). This questionnaire contains question on habitual activities with respect to occupation, leisure time, household, transportation means, and other daily activities. SQUASH has been shown to be a fairly reliable and valid tool to gauge the physical activity behavior of the general Dutch adult population(62). SQUASH will be measured at baseline, and at 6 and 12 months after surgery.
- Degree of immunoparalysis; Monocyte HLA-DR (mHLA-DR) expression is chosen based on previous studies showing that 1) mHLA-DR expression is greatly reduced on postoperative day 2, and 2) mHLA-DR expression at this timepoint has predictive value for postoperative infections. mHLA-DR expression will be determined on the following time-points: baseline, prior to surgery, day 2 and week 6 postoperatively. Differences in mHLA-DR expression between 1) prehabilitation and standard of care, and 2) before and after prehabilitation, will be explored. mHLA-DR expression will be measured using Quantibrite methodology (BD Biosciences). This allows for quantification of the absolute number of HLA-DR monoclonal antibodies bound to each monocyte (mAb/cell), which corresponds to the number of HLA-DR molecules expressed on the cell surface. This standardized method is considered the gold standard for HLA-DR analysis and has shown excellent precision, robustness, and predictive value for the development of infections. Blood will be preserved using PROT1 reagent (Smart Tube Inc.), frozen, and analyzed batchwise on a single flow cytometer.
- To compare preoperative health behavior between patients in the control group and patients in the intervention group, a short questionnaire will be developed for each group including questions on physical activity (e.g. number of physiotherapy visits).

## **8.5 Withdrawal of individual subjects**

Subjects can leave the study at any time for any reason if they wish to do so without any consequences. The investigator can decide to withdraw a subject from the study for urgent medical reasons.

### **8.5.1 Specific criteria for withdrawal (if applicable)**

Not applicable

## **8.6 Replacement of individual subjects after withdrawal**

Patients will not be replaced after withdrawal.

## **8.7 Follow-up of subjects withdrawn from treatment**

Regular follow up will be performed for all patients.

## **8.8 Premature termination of the study**

In case of significantly increased incidence of serious side-effects in patients within the intervention group, the study will be ended. Otherwise inclusion will continue. Serious side effects might be exercise related problems.

## **9. SAFETY REPORTING**

### **9.1 Temporary halt for reasons of subject safety**

In accordance to section 10, subsection 4, of the WMO, the sponsor will suspend the study if there is sufficient ground that continuation of the study will jeopardize subject health or safety. The sponsor will notify the accredited METC without undue delay of a temporary halt including the reason for such an action. The study will be suspended pending a further positive decision by the accredited METC. The investigator will take care that all subjects are kept informed.

### **9.2 AEs, SAEs and SUSARs**

#### **9.2.1 Adverse events (AEs)**

Adverse events are defined as any undesirable experience occurring to a subject during the study, whether or not considered related to trial procedure. All adverse events reported spontaneously by the subject or observed by the investigator or his staff will be recorded.

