## 2. OBJECTIVES

Primary Objective: To determine the effects of a multimodal intensive prehabilitation program a high-risk patient group on complications (Clavien Dindo score and Comprehensive Complication Index (CCI) score)

Secondary Objective(s): To investigate the effects of multimodal intensive personalized prehabilitation on an:

- Individual patient's level, i.e. length of hospital stay (in days), physical fitness (estimated  $VO_2$  peak, indirect 1 repetition measures, physical activity), nutritional status (body weight, fat-free mass, Patient-Generated Subjective Global Assessment (PG-SGA), mental health (HRQoL), intervention adherence
- Mechanistic level, i.e. innate immune response (degree of immunoparalysis)
- Hospital-efficiency level: costs due to complications, costs due to length of hospital stay, budget impact, cost-effectiveness
- Macro-economic level: changes in patients volumes, shifts in care between 2nd and 1st line healthcare

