#### 2. Preoperative period

##### A. Without intervention (standard preoperative care)

Patients will undergo standard preoperative care according to Dutch guidelines(39). To collect data, two additional appointments will be combined with regular, preoperative outpatient clinic visits. Patients will undergo measurements regarding physical fitness, nutritional status and health status as shown in Appendix I.

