### **2.B.2 Exercise program**

- Screening: all patients undergoing the multimodal intensive prehabilitation program will be screened for physical fitness according to the American College of Sports Medicine (ACSM) exercise preparticipation health screening questionnaire for exercise professionals. Patients screened at risk will be referred to a cardiologist or pulmonologist to undergo additional tests (e.g. ECG, spirometry, cardiopulmonary exercise test) to assess whether undergoing high intensity training (HIIT) during prehabilitation is safe.
- Assessment: the content of the exercise program will be adjusted based on a patient's estimated VO2 peak (submaximal Astrand-Rhyming test) and muscle strength (indirect 1RM).
- Goal: to increase physical fitness (estimated VO2 peak and indirect 1RM) by 10%.
- The content of the exercise program: to reach the goal, the exercise program consists of the following components:
  - *Endurance training*:
    - High intensity interval training (HIIT)
      - This supervised training (by 1st line physiotherapist) will be done
        - Group 'PREHAB LONG': two times a week
        - Group 'PREHAB SHORT': three times a week
      - The interval training duration is 28 minutes and performed with 4 intervals of moderate intensity (3 minutes) and 4 intervals of high intensity (4 minutes)
      - The workload is dosed at a percentage of estimated VO2 peak. High intensity is considered 90% of estimated VO2 peak
      - This interval training aims to reach levels of Borg 15-17 and >85%

of the age-predicted maximum heart rate, as long as the patient could effort the exercise

- Exercise may be performed on a bicycle, a rower, a treadmill and/or on other aerobic exercise machines

- *Resistance training*

- This supervised training (by 1st line physiotherapist) will be done
  - Group 'PREHAB LONG': two times a week
  - Group 'PREHAB SHORT': three times a week
- Strength training will be the same concept for all patients irrespective of VO2 peak
- The strength exercises are performed according to: 2 seconds of concentric strength and 2 seconds of eccentric strength.
- The strength training consists of two series of 10 repetitions of six exercises: leg press, chest press, abdominal crunch, lat pull down, low row and step up
  - In week 1 using 65% of calculated indirect 1RM (measured during assessment)

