  - In week 2 using 70% of calculated indirect 1RM (measured during assessment)
  - In week 3 using 75% of calculated indirect 1RM (measured during assessment)
  - In week 4 using 80% of calculated indirect 1RM (measured during assessment)
- The last bout with 10 repetitions needs to be attainable. If this is not the case in the next session dosing will be 5-10% lower. If in the last bout it appears that exercises are too low (≥15 repetitions will be achieved), in the next sessions dosing will be 5-10% higher

- *Homework/counseling*

- The homework will be done at the days without supervised training
- Patients are instructed to aim at 60 minutes walking and/or cycling a day. If possible, patients can do more than 60 minutes of walking or cycling every day
- In case of lower exercise capacity it is advised to walk/cycle 2-3 times a day for periods of 20 minutes
- Also an electric bicycle, a stationary bicycle and/or a walking aid

(walker) may be necessary

- Instructions on breathing techniques will be given to reduce the risk of developing pneumonia postoperatively

- *Rest*

- Patients are instructed to take care of recovery and adequate rest and sleep
- From 3 days before surgery no high intensity interval training and strength training are done. The patient will continue with the homework/counseling (walking/cycling every day) and the dietary supplements

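### Adverse events before surgery are captured passively, while contact is several-fold higher under intervention and it is unclear whether the training physiotherapists count as staff who record them

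*Protocol*

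**What the plan says.** Section 9.2.1 of the protocol: "All adverse events reported spontaneously by the subject or observed by the investigator or his staff will be recorded". Neither the outcome tables in 8.1 nor Appendix I lists an adverse-event question at any visit.

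Contact before surgery differs by condition. For prospective controls, section 5.1 (2.A) says: "To collect data, two additional appointments will be combined with regular, preoperative outpatient clinic visits". Under intervention, section 5.1 (2.B.2) adds supervised training: "Group 'PREHAB SHORT': three times a week" and "Group 'PREHAB LONG': two times a week". Training stops shortly before the operation: "From 3 days before surgery no high intensity interval training and strength training are done". Appendix I places baseline four or eight weeks before surgery and the second measurement one week before.

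The sessions are supervised by a first-line physiotherapist. No section says whether this person belongs to the investigator's staff, or how an event seen at training reaches the investigator.

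Section 8.8 ends the study if serious side-effects are significantly increased in the intervention group, and names exercise-related problems as a possible kind. Section 9.5 dispenses with a DSMB. In section 9.2.2, one class of serious event depends on the investigator's judgement, and the 15-day reporting period runs from the sponsor's first knowledge.

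**The concern.** When events are recorded only if volunteered or noticed, the chance of recording one rises with the number of occasions on which it could be mentioned or seen. Those occasions are unequal by design. A difference in non-serious preoperative events could then reflect contact rather than training.

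The bias could run either way. If the physiotherapists are staff, intervention patients are observed far more often and their events are captured more fully. If they are not, an exercise-related problem seen only at training has no stated path to the record or to the section 8.8 decision.

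This is a matter of data collection. An analysis plan written later cannot recover an event that nobody asked about or passed on.

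**Working it through.** The protocol gives no contact ratio or adverse-event rate, so there is no stated figure to reproduce. The contact imbalance can be rebuilt from the schedule.

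**Inputs**
- Control study appointments before surgery: 2 (section 5.1, 2.A).
- Measurement appointments under intervention: the same 2 (Appendix I).
- Supervised sessions per week: 3 in PREHAB SHORT, 2 in PREHAB LONG (2.B.2).
- Baseline 4 or 8 weeks before surgery (Appendix I), taken here as SHORT and LONG respectively. This mapping is an assumption; Table 3 says only under and over 5 weeks.
- No high-intensity or strength training in the last 3 days (2.B.2).
- Further assumptions: training starts at baseline, attendance is full, and endurance and resistance work share one session.

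**Formula:** ratio = (sessions + 2) / 2.

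**With the Appendix I timings**
- SHORT: (28 − 3)/7 × 3 = 10.7 sessions. Rounded down to 10, the ratio is 12/2 = 6.0; unrounded it is 6.4. Ignoring the 3-day stop, 12 sessions give 14/2 = 7.0.
- LONG: (56 − 3)/7 × 2 = 15.1 sessions. Rounded down to 15, the ratio is 17/2 = 8.5; unrounded it is 8.6. Ignoring the stop, 16 sessions give 18/2 = 9.0.

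The range is therefore about 6 to 9. Each week lost, for instance while a physician's approval is awaited under 2.B.1, lowers the SHORT ratio by 3/2 = 1.5 and the LONG ratio by 2/2 = 1.0.

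**Under other assumptions**

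| Assumption | SHORT | LONG |
|---|---|---|
| Exactly 5 weeks (upper limit for SHORT, lower limit for LONG) | (15+2)/2 = 8.5 | (10+2)/2 = 6.0 |
| 5 weeks, plus 2 regular visits counted in both conditions | (15+4)/4 = 4.75 | (10+4)/4 = 3.5 |
| 5 weeks, endurance and resistance on separate days | (30+2)/2 = 16 | (20+2)/2 = 11 |
| Short SHORT (2 weeks), long LONG (10 weeks) | (6+2)/2 = 4.0 | (20+2)/2 = 11 |

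These span roughly 3.5 to 16. Stacking extremes goes further: 2 weeks of SHORT with 2 regular visits in both conditions gives (6+4)/4 = 2.5. Contact is higher under intervention in every case.

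**What the ratio measures.** It counts occasions, not captured events, and training sessions count as occasions for staff to observe only if the physiotherapists are staff. If they are not, study appointments are 2 against 2, plus the intervention group's screening and non-exercise contacts.

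**Are they staff?** The text points both ways.
- Suggesting outside care: section 2 sets first-line against second-line care, "shifts in care between 2nd and 1st line healthcare", and the departments listed in 8.4 ("Study procedures are performed in the Radboudumc departments of Surgery, Urology, Neurosurgery, Orthopaedics" and others) do not include physiotherapy.
- Suggesting staff: section 9.5 has a first-line physiotherapist or dietician supervising the physical measurements, which are study data, and 11.4 speaks of hospital visits for training.

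**The case against.** The strongest reply is that section 9.2.1 already covers the physiotherapists. Section 9.5 has them or dieticians supervising study measurements, so they plausibly are staff and whatever they observe must be recorded. The list in 8.4 also omits dietetics and psychology, so the absence of physiotherapy shows little. This stands as far as it goes: the gap is an undefined duty, not an exclusion. It does not remove the imbalance, because on that reading staff see intervention patients several times as often as controls.

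Next, no planned analysis is biased. Adverse events are not a listed outcome and section 10 plans no comparison of them. This is right and limits the weight of the point. Section 8.8 nevertheless rests on an increase in one condition, which needs a like-for-like comparator.

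Appendix I is also not exhaustive: it leaves out baseline PG-SGA and the mHLA-DR samples, which other sections specify. Its silence alone would be weak evidence, but no other section describes an adverse-event question either.

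Three stronger readings are not supported.
- A reader might infer that the primary outcome is distorted. Complications are scored four weeks after surgery in both conditions, so this route does not touch them.
- A reader might take the expectation in 11.4 of finding more cardio-pulmonary conditions as proof of unequal capture. Those conditions are pre-existing, whereas 9.2.1 defines an adverse event as occurring during the study.
- A reader might multiply sessions across the trial and treat the total as harm. The documents give no capture probability per contact, so no number of missed events follows.

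**Conclusion.** The point holds in limited form, as a cheap improvement rather than a flaw in the main analysis. Passive capture combined with unequal contact allows recording of non-serious preoperative events, and of important medical events that need the investigator's judgement, to differ by condition.

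The contact imbalance is about 6 to 9 times with the Appendix I timings, on the assumptions listed, and roughly 3.5 to 16 times under others. It applies to prospective controls only; patients from the 24 retrospective months had no study contacts. The size and direction of any bias cannot be derived, because the physiotherapists' status is not stated. Deaths, admissions, postoperative complications and every listed outcome are unaffected. The practical stake is the section 8.8 decision in a trial without a DSMB.

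**What to change.** Amend section 9.2.1 in two places.

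1. Ask every prospective patient, in both conditions, one identically worded adverse-event question at the existing visit one week before surgery. Put it on the health-behaviour questionnaires, which section 8.4 says are still to be developed. Because a separate form is foreseen for each group, the identical wording has to be specified. Base any between-condition comparison of non-serious preoperative events on this source, in prospective patients only.
2. State that the training physiotherapists count as study staff for adverse-event reporting and must promptly pass training-related events to the investigator. Report these events descriptively and make them available for the section 8.8 decision.

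The cost is one added question and a small reporting duty, with no extra visit or committee. The remaining weakness is that the last week before surgery has no symmetric capture. A mandatory record review to close that gap would be more than this plan needs.
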